#### Secondary outcome analysis

Multilevel multivariate models will be constructed and validated as in the analysis of the primary outcome analysis. The survival time of residents will be analysed by a Cox model including a delayed input, a temporal axis representing age of admission in LTCF as its origin, and the situation with respect to the intervention coded by a time-dependant variable.

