**Fig. 1 Fig1:**
[figure not shown]
Flowchart representing the research design with a convergent parallel mixed-method

As depicted below in Fig. 2, over the course of the study timeline each of the 21 participating centres will be defined as a cluster and randomly allocated to one of the seven groups. This allocation will follow a sequence similar to the observational and interventional periods. Randomisation of LTCF will be stratified by region; each group includes LTCF from the three participating regions.

The strategy used addresses issues related to incomplete design by minimizing the collection load to preserve good power by removing uninformative combinations of clusters and periods without too much alteration of the power [44]. A sequence includes: one or two pre-intervention observational periods of two months; one delivery intervention period of three months followed by an interventional consolidation period of three months; then a short-term observational period of two months; and 12 months after intervention a final observational period of two months, called autonomy.

The individual data collection is based on an open cohort: as the study progresses, some residents will leave the LTCF or die (on average 25% each year, but likely higher for subjects requiring palliative care), while others will be admitted to the LTCF or begin to require palliative care and will be included at a later date.

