#### Primary outcome analysis

The data analysis will be based on the comparison of data collected during pre-intervention versus post-intervention periods. The three primary criteria will be tested according to a hierarchical procedure: identification sensitivity, access, and optimal timing from a fixed sequence procedure; constructed using a pre-specified sequence of hypotheses; and endpoints ordered according to their importance [62]. All tests will be performed at the 0.05 level following the pre-specified order. Once one hypothesis is tested and the results indicate it is not significant, all subsequent tests will not be performed.

The statistical model will take into account the non-independence of the observations, as multiple evaluations may concern the same resident across time due to the use of open cohorts and several residents are included from the same LTCF. This hierarchy (three levels) leads to the use of generalized linear mixed models (GLMM) for repeated measures [63]. For dichotomous outcomes (i.e. the patient has been identified or not), we will use a Bernoulli distribution with a logistic link function, and for continuous outcomes a normal distribution with identity link function. The independent variables will be: the LTCF and the resident considered as random factors, the calendar time interval (common to all groups) considered as a fixed factor, and treatment mode for the cluster in the time interval (pre-intervention = control, post-intervention = experimental) considered as a fixed factor associated with the effect of the intervention. The chronological sequence of stepped wedge randomized trials means that the number of clusters exposed to the intervention being tested increases as the trial progresses [41].

The observation of an intervention effect may reflect the existence of an underlying secular trend that is independent of the intervention. Therefore, modelling the background secular trend is necessary to remove bias in estimating the effect attributed solely to the intervention. However, the saturated time parameterization (by J-1 indicators if there are J periods) may not be the most efficient approach if there are a large number of periods relative to the number of waves and clusters due to the reduced degree of freedom available for estimating the intervention effect. Thus, we will use a parsimonious specification with a minimum number of parameters, such as a polynomial specification to a fixed degree [64].

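### The Cox model for resident survival, as specified, states no adjustment for calendar time and no allowance for clustering by LTCF

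*Protocol article*

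**What the plan says.** Under Secondary outcome analysis, the Protocol article gives two sentences. The first is general: "Multilevel multivariate models will be constructed and validated as in the analysis of the primary outcome analysis". The second concerns survival only. Survival time "will be analysed by a Cox model including a delayed input, a temporal axis representing age of admission in LTCF as its origin", with "the situation with respect to the intervention coded by a time-dependant variable". The Cox model thus has three stated features: delayed entry, an axis based on LTCF admission, and a time-dependent exposure.

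Under Primary outcome analysis, the model is a generalized linear mixed model with Bernoulli or normal outcomes. It has "the LTCF and the resident considered as random factors, the calendar time interval (common to all groups) considered as a fixed factor". The same section says that "the number of clusters exposed to the intervention being tested increases as the trial progresses" and that "modelling the background secular trend is necessary to remove bias in estimating the effect attributed solely to the intervention". It proposes a parsimonious form for the trend, such as a polynomial of fixed degree.

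**The concern.** Within each LTCF, intervention time comes after control time. Across the trial, the exposed person-time lies later in the calendar than the unexposed. A Cox model compares residents at the same value of its time axis. Whether that axis is read as age or as time since admission, two residents at the same point on it can be at very different calendar dates. The axis therefore does not remove a calendar trend, and a term for calendar time is needed. The article says as much for its primary analysis but does not repeat it for the Cox model.

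Residents of one LTCF share staff, case mix and local outbreaks. If that is ignored, the standard error can be too small.

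At stake is whether a change in mortality over the study, from whatever cause, is reported as the intervention lengthening or shortening life. The Background cites benefit without decreased survival in cancer care, so readers will look at this result.

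**Working it through.** The article gives no event count, power or HR for survival, so there is no figure of its own to reproduce. The check asks how large an apparent effect the model as listed would produce when the true HR is 1.

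**Inputs from the article:** 21 LTCF in seven groups; two pre-intervention periods of two months at most (4 months); delivery 3 months, consolidation 3 months, a final period of 2 months starting 12 months after the intervention; 25 eligible residents per average LTCF; residents leaving or dying "on average 25% each year, but likely higher for subjects requiring palliative care".

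**Assumptions:** exposure starts with delivery, giving 3 + 3 + 12 + 2 = 20 months exposed; groups start 1, 2 or 3 months apart; event rate 25% per year (the article's figure combines death and departure); mortality trend 0.8 to 1.25 per year; between-LTCF log-rate SD 0 to 0.4. A piecewise-exponential model on LTCF-months stands in for the Cox model.

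**Step 1: the calendar gap.** With 2-month steps the seven groups cross over at months 4, 6, 8, 10, 12, 14 and 16, and follow-up of all LTCF ends at 16 + 20 = 36. Taking one LTCF per group:
- Unexposed: total 70 months; mean calendar time = (sum of squared crossover times ÷ 2) ÷ 70 = (812 ÷ 2) ÷ 70 = 5.8 months.
- Exposed: total 7 × 36 − 70 = 182 months; mean calendar time = ((7 × 1296 − 812) ÷ 2) ÷ 182 = 22.7 months.
- Gap: 22.7 − 5.8 = 16.9 months.

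The same sum gives 14.6 months for 1-month steps and 19.0 for 3-month steps. If each LTCF is followed only in its own 4 + 20 = 24 month window, the gap is 24 ÷ 2 = 12 months.

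**Step 2: the apparent HR.** With no true effect, the HR without calendar time is approximately (yearly trend)^(gap ÷ 12). For example, 0.9^(16.9 ÷ 12) = 0.86 and 0.8^(16.9 ÷ 12) = 0.73. The exact ratio of average hazards is:

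| Follow-up | Gap (months) | Trend 0.9/yr | Trend 0.8/yr | Trend 1.25/yr |
|---|---|---|---|---|
| Own window only | 12.0 | 0.90 | 0.80 | 1.26 |
| All LTCF, 1-month steps | 14.6 | 0.88 | 0.77 | 1.32 |
| All LTCF, 2-month steps | 16.9 | 0.86 | 0.74 | 1.38 |
| All LTCF, 3-month steps | 19.0 | 0.85 | 0.71 | 1.44 |

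**Step 3: false positives** at nominal 5% (500 simulated trials per scenario, 2-month steps). A true 5% rate has a simulation standard error of √(0.05 × 0.95 ÷ 500), about 1 point.
- Intervention term only, all LTCF followed throughout: 25–33% at trend 0.9, 70–77% at 0.8, 92–94% at 1.25.
- Intervention term only, own window: 9–10% at 0.9 and 27–28% at 0.8.
- With linear and quadratic calendar time added, the apparent HR returns to about 1 (0.99 to 1.02) in every scenario.

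**Step 4: clustering.** This was taken separately, with calendar time already in the model. At between-LTCF SD 0.4, false positives were about 7–14% ignoring LTCF, 5–8% with an LTCF-robust standard error and 4–7% with LTCF fixed effects. At SD 0, ignoring LTCF gave about 4–7%. Leaving LTCF out did not move the HR.

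**The case against.** The strongest objection is that the Cox sentence directly follows "Multilevel multivariate models will be constructed and validated as in the analysis of the primary outcome analysis". One natural reading is that all secondary models inherit the primary structure, and that the Cox sentence adds only what is specific to survival. The wording lists what the model includes and need not be exhaustive. This is also a condensed article, and a full covariate list is often left to the analysis plan.

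Part of this stands. A reader might infer that the plan has decided to leave calendar time out, or that it treats residents as independent. The article does not say either; it is silent on both.

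The objection does not remove the point. The general sentence concerns multilevel models built like a Bernoulli or normal mixed model, and the Cox model is specified separately. Its terms do not carry over automatically: calendar time must enter as a second time-dependent quantity or as strata, and clustering needs a frailty or a robust variance. The article fixes the time axis, entry rule and exposure coding, yet not the adjustment that it elsewhere calls necessary.

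Three further limits are fair. The bias depends on the size of the trend and on the schedule, so it is not a fixed consequence of every secular change. It comes from the missing calendar term alone; LTCF is a standard-error matter. And survival is not among the listed secondary outcomes or hypotheses; it appears only in this analysis sentence.

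**Conclusion.** The concern holds as a gap in the specification. The Cox model as described states neither a calendar-time term nor an allowance for clustering by LTCF, and the preceding sentence does not clearly supply them. Fitted as listed, with a true HR of 1 and a mortality trend of 0.8 to 0.9 per year, it would show an HR of about 0.71 to 0.90. A rising trend gives a spurious HR above 1.

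These sizes rest on assumed trend, step length, event rate and follow-up window, and on a hazard that is otherwise flat; with no trend there is no bias. The clustering effect is material only if LTCF differ appreciably in mortality. A reader might also infer that the trial's main conclusion is at risk. It is not: the primary model includes both terms, and the survival analysis is secondary.

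**What to change.** State in the survival analysis, before the database freeze, that the Cox model includes:
- calendar time, as a time-dependent covariate in the same parsimonious form as the primary model, or as strata of the baseline hazard;
- an LTCF shared frailty or a cluster-robust variance. With 21 clusters, a robust variance needs a small-sample correction, since without one it stayed slightly above 5% in the check.

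The cost is a sentence or two of wording and a few lines of code. Coding a time-dependent intervention already needs calendar dates, so no new data are required. The interval for the HR will be somewhat wider, because part of the information in the before–after contrast is given up to the trend.

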### Qualitative analysis

A thematic content analysis [67] approach will guide the qualitative analysis of data, and continuous ascending coding will be privileged. The analysis will focus on both latent and manifest content. A team of three researchers with expertise in qualitative research will simultaneously conduct the qualitative analysis. To ensure a triangulated analysis approach, each of the three researchers will identify themes, build and validate the thematic tree. The unit of analysis will be the organisational level of each LTCF, considered as a case. NVivo software version 12 will facilitate qualitative data management, storage, and coding.

Pre- and post-implementation analysis will combine both interviews and observation data. The CFIR framework will guide the analysis of factors that shaped the implementation and sustainability of early integrated palliative care intervention.

### Integrative analysis

The qualitative and quantitative analyses will be completed with an integrative analysis that uses intra- and inter-cases to identify similarities and differences. This approach will enrich the understanding of any internal and external patterns and variances identified in each case.

The integration of qualitative and quantitative data will be carried out at each stage of analysis to perform an integrative analysis and interpretation. The results from the qualitative study will be triangulated with the results from the quantitative study, according to the research question being addressed, and will determine the integrative framework and different types of data that will be used and brought together in the analysis.

### Ethics approval and informed consent

Ethics approval for the conduct of this study was granted by the French Committee of Protection of Person (CPP), approval number 2020.09.06 bis 20.07.31.64318.

All participants (LTCF residents, family caregivers, and professionals) will be required to provide their informed consent in writing before their inclusion in the study. For residents who are unable to provide informed consent, this will be obtained from their legal representatives. Participant confidentiality will be ensured using codes and pseudonyms. De-identified data will be stored in protected computers and dedicated locked space. The use of databases and data processing are implemented in accordance with European regulations (General Data Protection Regulation - GDPR dated April 27, 2016).

## Discussion

Early integration of palliative care into the care pathway of older people is a challenging public health issue. To improve access to palliative care for people who are in need of such care, the integration of palliative care into the overall healthcare system is recommended [11]. This is a multicentre interventional study that aims to assess the effectiveness of early integrated palliative care on palliative care accessibility for older persons in LTCF and to identify the key factors for the successful implementation of early integrated palliative care and its sustainability in the LTCF context.

Previous studies have substantially demonstrated the benefits of early palliative care for patients with cancer [19, 20] and for their informal caregivers [68]. A wide range of strategies for integrating palliative care are recommended and shown to be effective [22, 23]. However, a pilot study conducted before designing the current project confirmed what is widely documented in the literature—there is an insufficient use of palliative care for the elderly, particularly for those with cognitive impairments [7] or with an absence of cancerous pathologies [26]. Evidence on the effectiveness of an early integrated palliative care approach for the elderly in LTCF is yet to be developed in France.

While factors limiting the development and implementation of palliative care are documented [69, 70], strategies for the integration of early palliative care in real-world LTCF settings were often overlooked. The mediating factors of the early integration of palliative care and its sustainability in LTCF contexts are poorly documented, if documented at all, in the French context. This study intends to provide relevant information on the effective integration of early palliative care in LTCF settings, as well as updated evidence on factors that influence the implementation process of early palliative care and its transferability across LTCF settings.

The development of the PADI-Palli intervention and its implementation utilises evidence-based guideline recommendations and theoretical frameworks from implementation sciences, and considers the practical issues experienced by those in LTCF by engaging key stakeholders. The use of this theory-based evidence-driven approach should increase both intervention effectiveness and transferability [33]. In addition, as recommended in interventional studies [71], our study uses a mixed-methods approach to overcome the challenges typically faced in these types of studies and interventional evaluations. The stepped wedge implementation design enables comparisons within (pre- and post-intervention) and between clusters (inter-sites). It maximises statistical power and allows the testing of whether an intervention is effective in real-world settings. The qualitative approach will enable a better understanding of relevant contextual factors that facilitate or hinder early integrated palliative care implementation, and it will underpin the reflection at the time of the implementation and assist with the consolidation of the intervention.

Although using the stepped wedge design in combination with a qualitative study can be logistically challenging, there are several advantages to this approach. Not only does this design include methodological and ethical considerations, but also it facilitates a better understanding of the study results, including changes or lack thereof, and the factors that contributed the results. This study is conducted in accordance with the trustworthiness and rigour criteria applied to the quantitative approach: internal validity, external validity, reliability, and objectivity [39]; and the qualitative approach: dependability, confirmability, credibility and transferability [72]. The publication of this paper describing the methodology and conduct of this study contributes to these validity criteria, including transferability.

The richness of the results from this multicentre interventional study has the potential to allow a better exploration and understanding of the contextual influences shaping intervention activities and outcomes of early integrated palliative care within LTFC. If proven effective, this intervention can be scaled to other care settings in which older persons require palliative care. The results will be disseminated through presentations at scientific conferences and professional meetings and publication in peer-reviewed scientific journals.

## Data Availability

Not applicable.
